**Methods:**

Sanquin Blood Bank is implementing ferritin-guided donation intervals to prevent donors from increasing iron loss at repeated donations. Using a stepped wedge cluster randomised trial approach, the design involves a random crossover of 29 clusters of blood collection centres from the existing policy without ferritin measurements to a ferritin-guided donation interval policy. This new policy includes ferritin measurements for all new donors and at every 5th whole blood donation, extending donation intervals to 6 months if ferritin is 15–≤ 30 ng/mL and to 12 months if ferritin is < 15 ng/mL. We measure ferritin levels of whole blood donors from stored plasma samples and collect haemoglobin levels and information on low-haemoglobin deferral and donor return from the donor database before, during and after the implementation period. We measure donor health during and after the implementation period using questionnaires, assessing physical and mental wellbeing and iron deficiency- and donation-related symptoms. We use multilevel analyses to investigate differences in ferritin and haemoglobin levels, low-haemoglobin deferral rates, donor return and donor health from whole blood donors, between blood collection centres that have versus those that have not yet implemented the ferritin-guided donation interval policy.

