### Study design

The FIND’EM study is a stepped wedge cluster randomised trial involving whole blood donors from all 50 fixed blood collection centres in the Netherlands. The stepped wedge cluster randomised design is increasingly being used in the evaluation of ‘service delivery type interventions’, which are bounded by logistical or policy constraints. A stepped wedge design is a one-way crossover trial in which several allocation groups start at different time points with the implementation of the new policy [14]. For FIND’EM, this involves random and sequential crossover of clusters from the current policy without ferritin measurements to the policy including ferritin-guided donation intervals, until all clusters are exposed to this new policy (Fig. 1). The numbers 1 to 29 have been randomly assigned to one of the 29 blood collection clusters. Allowing only a maximum of two clusters of a similar topographic region to each implementation step, the two clusters with the lowest numbers from each region were allocated to step 1, the clusters with the third and fourth lowest numbers from each region were allocated to step 2, the clusters with the fifth and sixth lowest numbers from each region were allocated to step 3 and the remaining clusters were allocated to step 4. The allocation was not concealed and the planned timing of crossover of all blood collection clusters was revealed before the start of the implementation period. In November 2017, Sanquin started with implementing ferritin-guided donation intervals in eight clusters of blood collection centres (28% of all blood collection centres). The next three implementation steps were planned for May 2018, October 2018 and February 2019. The number of repeat whole blood donors with low ferritin levels appeared to be higher than anticipated. Therefore, to ensure sufficient blood supply in The Netherlands, further implementation had to be delayed and executed in smaller steps. The second step of implementation thus included four clusters of collection centres from different topographic regions (step 2a), instead of the planned eight clusters, and was scheduled for May 2018. The remaining clusters of step two implemented ferritin-guided donation intervals in October 2018 (step 2b). The third step was again split into two implementation waves, in which four clusters implemented the policy in March 2019 (step 3a) and three additional clusters of step 3 started in October 2019 (step 3b). Due to logistical reasons, one cluster randomised to step 3 was not able to implement the ferritin-guided donation intervals in October 2019. The fourth and final step included the remaining six clusters of collection centres and was executed in November 2019 (Fig. 1). On average, a total of 1275 whole blood donations are done at collection centres of each implementation step per week. Effectively, this stepwise strategy results in a gradual increase of the intervention group and a simultaneously decreasing control group. This implementation strategy and the ferritin-guided donation interval policy itself was approved by Sanquin’s Board of Directors after review and approval by Sanquin’s Medical and Ethical Advisory Boards. Additionally, Sanquin’s Ethical Advisory Board has approved the FIND’EM protocol for additional questionnaires and ferritin measurements. As part of standard practice, blood donors are asked for consent for their unusable remainder of the donation to be used for medical scientific research. Consent for the use of this material was included in the ethical approval for the current study. All research activities commenced after ethical approval was obtained. All participating donors who filled in a questionnaire provided additional written informed consent. As the FIND’EM study is a minimal risk study, a data monitoring committee is not needed.

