### Study population

Both new (i.e. a donor undergoing pre-donation screening) and repeat donors (i.e. a donor making a whole blood donation or attempt) are eligible to participate in this study. The intervention likely results in delayed effects. Ferritin levels of a donor visiting a blood collection centre where the intervention has been implemented will only be measured every fifth donation. Furthermore, the extension of donation intervals makes it necessary to allow the blood collection centres to be exposed to the intervention for a certain amount of time before donors return and the effectiveness of the new policy becomes observable. We therefore selected three measurement time points: (1) before implementation (i.e. baseline), (2) mid-implementation (when 55% of blood collection centres had implemented the policy) and (3) after complete implementation of ferritin-guided donation intervals. As Sanquin had already started the implementation of the ferritin-guided donation intervals in November 2017, before approval from the Ethical Advisory Board for the FIND’EM study, we were unable to collect questionnaire data from donors at baseline. However, baseline data on other outcomes (Hb and ferritin levels, low-Hb deferral and donor return) are measured after ethical approval in stored samples, and a large majority of the donors (99%) provide their consent to the routine request to ‘make the unusable remainder of my donation available for medical scientific research in general’ (Fig. 2). Whole blood donors who visit one of the 50 fixed blood collection centres during a pre-selected week at mid-implementation or after complete implementation are asked to participate by completing questionnaires. This makes the current study an open cohort design study with repeated cross-sectional measures and new samples at each measurement. Donors registering at the registration desk of one of the collection centres during one of these time points will receive a leaflet with information on why this study is performed, explaining that upon participation, the donor is asked to fill in a questionnaire and participation is voluntary, the leaflet contains contact details of the research team in case of any questions and a link to the study website with additional information and frequently asked questions. The donor is asked to read the study information while waiting for their health check. After the check, the donors will be asked whether they have read the study information. If the donor decides to participate, an informed consent form will be signed and the donor physician or nurse will sign the form as a representative of the researcher. Donors who decide not to participate are asked to write down the reason for non-participation.

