### Control condition

Before each whole blood donation, a donor is seen by one of the doctors or nurses to check haemoglobin levels and blood pressure and screen for any indications a donor might not be eligible to donate whole blood at that moment. Sanquin’s current guidelines include Hb cut-offs for donor eligibility of > 13.5 g/dL for men and > 12.5 g/dL for women, which is in accordance with the international guidelines and European legislation [15]. Donors with low Hb (measured prior to donating in capillary blood with HemoCue 201, Angelholm, Sweden) are deferred from donating for 3 months.

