### Data collection

Pseudonymized data on age, sex, Hb levels and deferrals will be extracted from the donor database (eProgesa software application; MAK-SYSTEM) for all new and repeat whole blood donors who visit a fixed blood collection centre during a pre-selected week at one of the three measurement time points and gave consent for their information and left-over material to be used for research purposes. Furthermore, we will calculate donor return rates as the percentage of donors with a donation attempt within 6 months after the next allowed donation date. We will use stored plasma samples of new donors and repeat donors who made a donation attempt at one of the fixed blood collection centres during one of the pre-selected measurement time points to determine ferritin levels in intervention and control groups. Ferritin will be measured on the Architect i2000sr (Abbott Diagnostics) from donation samples collected in K3EDTA tubes (Greiner) and stored at − 30 °C. After storage, ferritin levels may be lower than those in fresh samples [16]. Within the FIND’EM study, we will compare ferritin levels of donors donating at centres where the ferritin-guided donation interval policy was implemented to ferritin levels of donors donating at centres where the policy was not implemented yet. For both groups, we will use samples that were stored for the same time period. Therefore, we expect similar decreases of ferritin levels as a result of storage in both groups, still allowing this comparison. For the validation of ferritin levels from stored samples of donors participating in the FIND’EM study, we will compare ferritin levels from stored samples with ferritin levels measured in fresh samples as part of the ferritin-guided donation interval policy.

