### Sample size calculations

Using data from the first clusters of blood collection centres that have implemented the ferritin-guided donation intervals, we found a mean increase in ferritin levels of 4 ng/mL (standard deviation (SD) 54 ng/mL) over a 6-month period. To detect a difference of 4 ng/mL, assuming a SD of 54 ng/mL, a two-sided significance level of 5%, a power of 80% and ignoring the correlated observations, a sample size of 5720 subjects is needed. We used the following formula to calculate the actual sample size:
$$ m=\frac{N}{1+\left(n-1\right)\left(1-\rho \right)} $$

where *m* = number of blood collection centres, *N* = sample size ignoring the correlated observations; *n* = average number of subjects within a blood collection centre and *ρ* = intraclass correlation coefficient. Assuming an average number of subject within each blood collection centre of 150 and an intraclass correlation coefficient of 0.1, we need 42 centres in total. With the fixed number of 50 blood collection centres (i.e. 7500 subjects), the power of the study is more than enough to detect the difference of 4 ng/mL. An individual autocorrelation coefficient is not included in our sample size calculation as we include repeated cross-sectional measures. With approximately 7500 donation attempts at fixed collection centres each week, we anticipate that we will be able to collect data on age, sex, Hb levels and deferrals and ferritin levels of approximately 7500 donors at baseline, mid-implementation and after implementation, thereby including more than sufficient data to reliably investigate the effectiveness of the ferritin-guided donation intervals. Furthermore, during data collection at mid-implementation, approximately 3500 donors filled in the questionnaires. We expect about the same response for the data collection after full implementation of the new policy.

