The use of a stepped wedge cluster randomised trial approach allows to implement and simultaneously evaluate the policy. As data collection takes place at multiple time points during the implementation period, all blood collection centres contribute data under both the control and intervention condition. Furthermore, this design makes it possible to investigate the effects as if it was a randomised controlled trial by correcting for time and clustering of donors and blood collection centres. This design also introduces some challenges, including prolonged trial duration compared to a standard randomised controlled trial, time-varying confounding, instructing all parties involved, making sure each cluster is committed and performing the assigned policy, and communication with whole blood donors [14, 21]. Furthermore, the lack of blinding to the allocation for both participants and trial staff may introduce a risk of bias [22]. Recruitment bias for the questionnaire data is limited by inviting all eligible donors at the different measurement time points to participate. For other outcomes, all available information from donors who gave consent for their unusable remainder of the donation to be used for medical scientific research was used in the current study. Detection bias is expected to be minimal because outcome assessment does not include any judgement from the researchers [22]. For our sample size calculation, we considered multiple clustering effects that may be present in our study design. An individual autocorrelation coefficient will not affect our sample size as there are no repeated measurements from the same participants. As participants in the same cluster are more alike than participants in another cluster, we included an intraclass correlation coefficient of 0.10. Finally, it may be necessary to take into account a cluster autocorrelation coefficient. However, the cluster autocorrelation coefficient may be difficult to determine and the impact on the total sample size is probably limited [23]. Although the appropriate sample size calculation for stepped wedge designs is still subject of discussion, it is a potential limitation that we did not take into account a cluster autocorrelation coefficient in our sample size calculation. The setting of Sanquin as one organisation with multiple blood collection centres has some advantages in the execution of a stepped wedge cluster randomised trial compared to locally organised general practices or hospitals, for example. The blood collection centres are randomised to implementation steps and instructed to perform the assigned policy, with centralised organisation and monitoring. To our knowledge, this method has never been used in transfusion-related research. The effectiveness of the ferritin-guided donation interval policy on Hb and ferritin levels, Hb deferral rates, donor return rates and donor health likely has a delayed response, because (1) donors’ ferritin levels are only measured when they make a fifth donation and (2) the policy involves donation interval extension which delays follow-up. Delaying the implementation period of ferritin-guided donation intervals should therefore have minimal negative impact on the outcome of the study. Sanquin’s Ethical Advisory board approved the FIND’EM study protocol after the start of the implementation period and we were therefore not able to collect baseline questionnaire data in September 2017. Furthermore, this together with logistic constraints made it impossible to collect data at each implementation step. Therefore, we might have less detailed data on the effects of the new policy on the outcomes over time compared to a design with outcome measurements at each cross-over period. The secondary outcome donor health is measured at mid-implementation and after complete implementation. Investigating the effectiveness of the ferritin-guided donation intervals policy on donor health is limited to the use of questionnaire data collected at mid-implementation and after the implementation period. Data on ferritin levels is available at baseline, mid-implementation and after complete implementation of the policy.

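### The reason given for not measuring at each implementation step does not fit Hb and low-Hb deferral, and using only three database weeks gives up precision that an added extraction could recover

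*Protocol article*

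**What the plan says.** The Abstract (Methods) states that the investigators will "collect haemoglobin levels and information on low-haemoglobin deferral and donor return from the donor database before, during and after the implementation period". The Control condition section shows that Hb is a routine entry: "Before each whole blood donation, a donor is seen by one of the doctors or nurses to check haemoglobin levels". Data collection then limits the extraction of Hb and deferrals to donors "who visit a fixed blood collection centre during a pre-selected week at one of the three measurement time points". Study population says that "baseline data on other outcomes (Hb and ferritin levels, low-Hb deferral and donor return) are measured after ethical approval in stored samples", and adds that 99% of donors give the routine research consent.

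Two reasons are given for three time points. Study population argues that effects are delayed, because ferritin is measured only at every fifth donation and intervals are then extended. The Discussion adds that late ethical approval matters too: "this together with logistic constraints made it impossible to collect data at each implementation step". It concedes less detailed information on how effects develop over time, but does not mention precision. Sample size calculations concludes that the three weeks give "more than sufficient data to reliably investigate the effectiveness of the ferritin-guided donation intervals".

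**The concern.** Late approval and logistics can prevent a questionnaire from being handed out, and may limit how many stored samples are assayed. They do not prevent a retrospective query of Hb and deferral records, which is how the plan obtains its September 2017 baseline. The stated obstacle therefore does not apply to these two outcomes.

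At baseline no cluster is exposed, and at the last time point all are. Only the mid-implementation week, with 16 exposed and 13 unexposed clusters, compares the policies at the same calendar time. Separation of the policy effect from time trends, which the Discussion itself names as a challenge, leans on that one week. The statement that the data are more than sufficient comes from a ferritin calculation; none is shown for deferral.

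**Working it through.** **The plan's own figure.** Total N = 4 × (1.960 + 0.842)² × 54² / 4² = 5722, against 5720 stated. The plan's formula then gives 5720 / (1 + 149 × 0.9) = 42.3, against 42 centres. Both reproduce. They concern ferritin only, and neither reflects how many weeks contain both policies. The form of the centre formula is a separate matter and is not used below.

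**Inputs.**
- Waves (Study design): the first step was "implementing ferritin-guided donation intervals in eight clusters of blood collection centres" in November 2017, followed by 4 (May 2018), 4 (October 2018), 4 (March 2019), 3 (October 2019) and 6 (November 2019). The sum is 29.
- Mid-implementation at 55% (Study population): 16/29 = 55%, so after the October 2018 wave.
- Visits (Sample size calculations): 7500 / 29 = 258.6 per cluster-week.
- Intraclass correlation (ICC): the plan's 0.1, varied. Cluster autocorrelation (CAC): not given; 1 matches the plan's random-intercept model, and lower values are assumptions.

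**Formula.** For a random cluster intercept, categorical weeks, a binary exposure X and CAC 1, in SD units:

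Var = Iσ²(σ² + Tτ²) / [(IU − W)σ² + (U² + ITU − TW − IV)τ²]

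Here I = 29 clusters, T = weeks, τ² = ICC = 0.1 and σ² = 0.9/258.6 = 0.00348. U is the sum of X, W the sum of squared week totals, and V the sum of squared cluster totals.

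*Three weeks (0, 16, 29 exposed).* U = 45; W = 256 + 841 = 1097; V = 16×4 + 13×1 = 77.
IU − W = 208; second bracket = 2025 + 3915 − 3291 − 2233 = 416.
Var = 0.1009 × 0.3035 / (0.72 + 41.6) = 0.000724, so SE = 0.0269.

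*Seven weeks (0, 8, 12, 16, 20, 23, 29 exposed).* U = 108; W = 2234; V = 288 + 100 + 64 + 36 + 12 + 6 = 506.
IU − W = 898; second bracket = 11664 + 21924 − 15638 − 14674 = 3276.
Var = 0.1009 × 0.7035 / (3.13 + 327.6) = 0.000215, so SE = 0.0147.

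The variance ratio is 3.37. Precision lost is 1 − 1/3.37 = 70%, and the SE is √3.37 = 1.84 times wider.

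**Sensitivity (generalised least squares on cluster-week means).**

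| Assumption | Precision lost |
|---|---|
| Immediate effect, ICC 0.001-0.2, CAC 0.5-1 | 70-73% |
| Immediate effect, linear time in months | 72% |
| Immediate effect, October and November 2019 waves share one week | 65-69% |
| First 6 months of exposure dropped | 64-65% |
| Effect starts only after 6 months | 53-57% |
| Effect ramps up over 12 months | 47-51% |
| Effect grows linearly with exposure | 44-48% |
| Immediate effect, equal total observations, ICC 0.1, CAC 1 | 31% |

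The three delayed-effect rows use ICC 0.005-0.1 and CAC 0.9-1. They place the weeks at assumed months −2, 5.5, 10.5, 15.5, 22.5, 23.5 and 24.5 from November 2017 (three-week design: −2, 15.5, 24.5). Across them the SE is 1.33-1.53 times wider.

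**Deferral.** The documents give no deferral rate. At an assumed 3%, the difference detectable with 80% power is 2.802 × SE × √(0.03 × 0.97). With an immediate effect:
- ICC 0.1, CAC 1: SE 0.0269 v 0.0147, giving 1.29 v 0.70 percentage points.
- ICC 0.1, CAC 0.8: SE 0.0686 v 0.0375, giving 3.28 v 1.79 points.

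Over ICC 0.005-0.1 and CAC 0.8-1 the range is about 1.3-3.3 points with three weeks and 0.7-1.8 with seven.

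**The case against.** The strongest reply is that Study population gives a design reason that has nothing to do with feasibility: effects are delayed, so centres need time under the policy before measurement. This is fair. It rules out quoting 70% without qualification, since that figure assumes an immediate constant effect. It does not justify omitting the intermediate weeks, because 44-57% is still lost when the delay is modelled. Nor do the chosen weeks avoid short exposure: Trial status plans the last collection for the end of November 2019, the month in which the final six clusters crossed over.

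A second reply is that seven weeks hold 7/3 = 2.3 times as many visits, so much of the gain is volume. That also stands: with equal totals the loss is 31% at ICC 0.1 and CAC 1. These visits, however, need no new donor contact or assay.

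Third, the Discussion already discloses a limitation. It does so for detail over time, not for precision, and it presents the limit as unavoidable.

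A reader might extend the point to donor return, since it too comes from the database. The documents do not support that without more work. Return is "the percentage of donors with a donation attempt within 6 months after the next allowed donation date". Adding 6 months to a minimum interval of 56 or 120 days gives roughly 8 or 10 months, while waves are 1 to 7 months apart. Many added control visits would have follow-up that runs past their cluster's crossover, and the calculation above ignores this.

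**Conclusion.** The point holds for Hb and low-Hb deferral. The claim that data at each step could not be collected is too broad for these outcomes, and the three-week restriction costs about 44-57% of the precision of a one-week-per-wave design under the delayed response that the plan expects. The 70% figure is the immediate, constant-effect case.

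Availability at every visit is inferred from the Abstract, Control condition and Data collection sections. The delayed-effect figures rest on assumed week timings, and the CAC values are assumptions.

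Two stronger readings should be resisted. One is that most of the information on three of the four outcome groups is lost: the first group includes ferritin, which needs assays, and the gain for donor return has not been shown. The other is that the trial is underpowered for deferral: the documents give neither a deferral rate nor an ICC for it, so the detectable differences only illustrate the range.

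**What to change.** - For Hb and low-Hb deferral, extract at least one database week in each interval between executed waves, preferably late in the interval: before November 2017, then after the November 2017, May 2018, October 2018, March 2019, October 2019 and November 2019 crossovers.
- Analyse these outcomes with categorical period and with exposure duration since the cluster's own crossover.
- If more than one week per interval is used, account for repeat visits by the same donor; the Discussion currently assumes there are none.
- Keep the three-week analysis for ferritin and the two-week analysis for questionnaires.
- Add donor return only with a stated rule for visits whose return window spans the cluster's crossover.
- Reword the Discussion so that impossibility refers to questionnaires and, if it applies, ferritin.

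The cost is a wider query, some programming, confirmation that the existing approval and routine consent cover the added weeks, and a model that handles short exposures. No donor contact or new assay is needed.
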